In addition, it is reported that the failure rates of conventional balloon angioplasty for the infrapopliteal arteries range from 10% to 40% depending on lesion type and surgeon’s experience. Besides, in case of severe calcification, residual stenosis ≥50%, dissection leading to blood flow disturbances, or occlusive thrombus formation not responsive to thrombolysis, thrombus aspiration or balloon angioplasty, stenting is usually attempted following balloon angioplasty. Because of concern about early thrombus formation resulting from stent placement in the small-diameter infrapopliteal arteries and possible late lumen loss caused by intimal hyperplasia, routine stenting in the infrapopliteal arteries are not being widely spread.

The self-expanding nitinol stent for the below-the-knee arteries were developed for the purpose of maintaining stable blood flow, preventing lumen loss and ultimately improving vascular patency rate. When the self-expanding stent was implanted in 16 patients with critical limb ischemia who were not respond to conventional balloon angioplasty, the vascular patency rate at 6 months was obtained from 14 patients of them, and good patency was observed in 12 lesions.

In a study of below-the-knee artery balloon angioplasty followed by routine (self-expanding) stenting in 47 patients with critical limb ischemia as it was expected that it would contribute significantly to good clinical outcomes, it was found that the vascular patency and limb salvage rates were 76.3% and 95.9% at 12 months, and 54% and 90.8% at 24 months, respectively

As mentioned above, with the recent advances of medical technologies and the introduction of self-expending stents only for the infrapopliteal arteries, vascular interventions in critical limb ischemia are radically developing. However, the gold standard therapy has not been established yet like that for coronary artery interventions. Moreover, there is currently a lack of comparative studies of balloon angioplasty alone *versus* balloon angioplasty with routine stenting – the former is that it is left as it is in the case of good responses to balloon angioplasty and the latter is that stenting is routinely conducted after balloon PTA, similarly to coronary artery intervention.

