**Participating centers:**

|  | Participating centers (sites) | Principal investigators | Co-investigators |
| --- | --- | --- | --- |
| **1** | Korea University Guro Hospital | [name] | [name] |
| **2** | Kwandong University MyoungJi Hospital | [name] |  |
| **3** | KonKuk University Chungju Hospital | [name] |  |
| **4** | Soonchunhyang University Cheonan Hospital | [name] | [name] |
| **5** | Yonsei University Shinchon Severance Hospital | [name] | [name] |
| **6** | Yonsei University Gangnam Severance Hospital | [name] |  |
| **7** | KyungHee University Medical Center | [name] |  |
| **8** | Gachon University Gil Hospital | [name] | [name] |
| **9** | Sam Medical Center, AnYang | [name] | [name] |
| **10** | SamSung Medical Center | [name] |  |
| **11** | Eulji University Hospital | [name] |  |
| **12** | Sejong General Hospital | [name] | [name] |
| **13** | Incheon Sarang Hospital | [name] |  |
| **14** | Pusan National University Hospital | [name] |  |

1. **Inclusion/Exclusion Criteria**

*a. Inclusion criteria*: All of the criteria listed below shall be met.

1. Clinical criteria
   1. Age 20 years of older
   2. Symptomatic critical limb ischemia (Rutherford 4 - 6)
   3. Patients with signed informed consent
2. Anatomical criteria
   1. Target lesion length < 8 cm by angiographic estimation
   2. Stenosis of >50% or occlusive atherosclerotic lesion of the ipsilateral infrapopliteal artery
   3. Reference vessel diameter should be 2.0–4.5 mm.

*b. Exclusion criteria:*

1. Clinical criteria
   1. Patient has a known allergy to heparin, aspirin, or other anticoagulant/antiplatelet therapies or a bleeding diatheses or is unable, or unwilling, to tolerate such therapies
   2. Patient takes warfarin
   3. Patient has a history of previous life-threatening contrast media reaction
   4. Patient is currently enrolled in another investigational device or drug trial
   5. Patient is currently breast-feeding, is pregnant, or intends to become pregnant
   6. Patient is mentally ill or retarded
   7. Acute critical limb ischemia
   8. Major bleeding history within prior 2 months
   9. Age > 80 years
   10. Severe hepatic dysfunction (> 3 times normal reference values)
   11. Serum creatinine level ≥ 3.0 mg/dl or dependence on dialysis

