1. Imaging parameter (CT, color Doppler): >50% restenosis at 12 months
2. Hemodynamic parameter: Ankle-brachial index, Calf-brachial index, Thigh-brachial index
3. Clinical outcomes/course:
   1. Symptom recurrence or aggravation
   2. Target vessel revascularization
   3. Major cardiovascular adverse events : death, MI, stroke
   4. Lower limb amputation status
4. **Efficacy Evaluation Criteria/Method and Analysis Techniques**

1. Primary endpoint: Binary restenosis at 12 months

Binary restenosis : >50% re-obstruction of the target lesion as assessed by quantitative

angiography

2. Secondary endpoints

1. Target vessel revascularization rate
2. Limb salvage rate: free from amputation
3. Major cardiovascular adverse events : death, MI, stroke
4. Angiographic variables (Binary restenosis, FU MLD, LL, % restenosis)

3. Statistical analysis

Categorical variables will be expressed in percentage, and inter-subgroup comparisons will be analyzed with either Chi-square or Fisher’s exact test. Continuous variables will be expressed in mean ± standard deviation, and inter-subgroup comparisons will be analyzed with Student’s *t* test. In addition, clinical course and outcomes including patient’s symptoms, restenosis assessed based on the findings on ABI and invasive angiograms, target vessel revascularization, major cardiovascular adverse events (death, MI and stroke) and lower limb amputation status will be analyzed with Kaplan-Meier survival estimates, and inter-subgroup comparisons will be analyzed with log-rank test. *p* value <0.05 will be considered statistically significant.

1. **Data Management**

In order to ensure confidentiality of research data, all the personal information of patient data collected will be encoded, recorded and kept so that they cannot be disclosed easily. Additionally, all electronic (computed) data will be saved in a computer to which access will be restricted, and all documentary data will be stored in a locking system.

1. **Study Implementation Plan**

|  | 2011  11 |  |  | 2012  9 |  |  | 2013  8 |  |  |  | 2014  11 | 2015  1 |
| --- | --- | --- | --- | --- | --- | --- | --- | --- | --- | --- | --- | --- |
| Patient enrollment |  |  |  |  |  |  |  |  |  |  |  |  |
| Data collection and analysis |  |  |  |  |  |  |  |  |  |  |  |  |
| Paper Writing |  |  |  |  |  |  |  |  |  |  |  |  |

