**Alpha**

Another factor that has an impact on the required sample size is alpha, the criterion used for statistical significance. We used an alpha of 0.05, which is often the default value, in computing the required sample size of 89 per group.

It is sometimes appropriate to select a more conservative criterion. For example, with alpha set at 0.01 the required sample size would be 132 per group. Conversely, it is sometimes appropriate to select a less conservative criterion. For example, with alpha set at 0.10 the required sample size would be 70 per group.

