**Tails**

The final factor we need to consider is whether the significance test is one-tailed or two-tailed. We assumed that the study will use a two-tailed test, which is usually appropriate, and computed the required sample size as 89 per group.

If it were appropriate to use a one-tailed test (with alpha at 0.05) the required sample size would be 70 per group.

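### Follow-up MLD is compared by an unadjusted t test although reference vessel diameter is known at entry; late loss should be read as subordinate to follow-up MLD

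*Combined protocol and SAP*

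**What the plan says.** Under Efficacy Evaluation Criteria/Method and Analysis Techniques, the fourth secondary endpoint is a group of measures: "Angiographic variables (Binary restenosis, FU MLD, LL, % restenosis". LL is neither expanded nor defined there. The nearest wording is in Backgrounds, which mentions "possible late lumen loss caused by intimal hyperplasia" as a worry about stenting small infrapopliteal arteries.

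The Statistical analysis paragraph has one rule for such measures: "Continuous variables will be expressed in mean ± standard deviation, and inter-subgroup comparisons will be analyzed with Student’s" t test. It names no covariate. The threshold is the same throughout: "value <0.05 will be considered statistically significant". Nothing says which angiographic measure governs if they disagree.

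The anatomical inclusion criteria state "Reference vessel diameter should be 2.0–4.5 mm". The comparator, in Study Design and Methodology, is balloon angioplasty with provisional stenting, so some control patients may also receive a stent.

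**The concern.** Two features of the continuous angiographic analysis deserve attention.

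First, precision. Eligible vessels differ more than twofold in reference diameter (4.5/2.0 = 2.25). A larger vessel will tend to have a larger lumen at 12 months in either arm. A plain t test leaves that variation in the error term, although the diameter has to be known at entry.

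Second, interpretation. If LL means post-procedure minus follow-up MLD, its starting value is measured after the randomised treatment. The arms then need not start level. An arm that gains more lumen at the procedure has more to lose, and it can show a larger loss while still having the wider lumen at 12 months. At stake is the reading of one secondary variable: a p value for late loss could point against the arm with the better final lumen, and the plan does not say how to resolve the conflict.

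**Working it through.** **The plan's own figures.** The documents give no mean, SD or power for MLD or LL. The only sample size is for the primary endpoint: 55% against 75%, two-sided alpha 0.05 (Appendix, Alpha and Tails), 80% power. The pooled-variance formula without continuity correction gives 88.1, rounded up to 89 per group, as stated. Enrolment is 116 per group with 30% loss expected, so about 116 × 0.70 = 81 per arm would be evaluable. I use 81 below. All values in mm and all correlations are assumptions.

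**1. Precision of the follow-up MLD comparison.** With correlation r between reference diameter and follow-up MLD, ANCOVA multiplies the residual variance by 1 − r², and the equivalent gain in sample size is 1/(1 − r²).

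| r | Variance factor | Variance cut | Equivalent gain in patients |
|---|---|---|---|
| 0.4 | 0.84 | 16% | 1/0.84 = 1.19, or 19% |
| 0.6 | 0.64 | 36% | 1/0.64 = 1.56, or 56% |

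In terms of power, take an SD of 0.8 mm. The unadjusted standard error is 0.8 × √(2/81) = 0.126 mm. With adjustment the SD becomes 0.8 × √0.84 = 0.733 or 0.8 × √0.64 = 0.640. Power is Φ(f/SE − 1.96), where f is the true difference in follow-up MLD.

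| f (mm) | t test | ANCOVA, r = 0.4 | ANCOVA, r = 0.6 |
|---|---|---|---|
| 0.2 | 36% | 41% | 51% |
| 0.3 | 66% | 74% | 85% |

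**2. When late loss reverses.** Let g be the stent arm's advantage in post-procedure MLD and f its advantage in follow-up MLD. With LL = post-procedure MLD − follow-up MLD, the arm difference in mean LL is g − f. The stent arm shows more loss despite a wider follow-up lumen only if g > f > 0.

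**3. How likely a significant reversal is.** The chance that LL is significantly larger in the stent arm is Φ((g − f)/SE − 1.96). For an LL SD of 0.7 mm, SE = 0.7 × √(2/81) = 0.110 mm. Suppose both arms lose half of their acute gain, so that f = g/2. If a proportion c of controls is stented and responds like the stent arm, the difference shrinks to (1 − c)(g − f).

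| g, f (mm) | g − f | c = 0 | c = 10% | c = 40% |
|---|---|---|---|---|
| 0.3, 0.15 | 0.15 | 28% | 23% | 13% |
| 0.4, 0.20 | 0.20 | 44% | 37% | 19% |
| 0.5, 0.25 | 0.25 | 62% | 53% | 28% |

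The values of c span the 10% to 40% balloon failure range quoted in Backgrounds. Using that range as the provisional stenting rate is my assumption.

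A simulation with LL SD 0.755 mm and no control stenting gave 39% for g = 0.4, f = 0.2 and 71% for g = 0.6, f = 0.3. With 30% of controls stented these fell to 23% and 41%. Without a post-procedure excess the reversal disappears: 2.4% for g = f = 0.3, and 0.3% for g = 0.2, f = 0.3.

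**4. Adjustment does not repair late loss.** Adjusting LL for post-procedure MLD returns the follow-up MLD comparison with the sign reversed: in a test fit the arm coefficients were +0.128 for LL and −0.128 for follow-up MLD. It also conditions on a variable that treatment may affect. The remedy is therefore to change which variable leads.

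**The case against.** The strongest defence has four parts.

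- An unadjusted t test is valid in a randomised trial, and the correlation of 0.4 to 0.6 is not in the documents. This stands: the gain is in efficiency, and it would be small if the correlation were low.
- A reader might infer that the plan will probably declare stenting worse on late loss. The documents do not support that. They give no diameters, loss fractions or SDs and do not say that the stent arm starts with a wider lumen. The higher figures also assume the same proportional loss in both arms; a stent that lost a smaller fraction would bring f closer to g or above it. Provisional stenting in controls dilutes the effect further.
- A reader might also infer that a late-loss result against the stent would contradict the trial's aim. Prevention of lumen loss appears in Backgrounds as the reason the device was developed, whereas the hypothesis in Study Objectives concerns restenosis rate. Backgrounds also names late lumen loss as a worry about stents, so comparing it between arms answers a relevant question. More loss and a wider final lumen can both be true. This argues for keeping late loss in the report.
- Follow-up MLD, percent restenosis and the primary binary restenosis do not subtract the post-procedure diameter, so a contradiction would be visible. This also stands and limits the consequence to possible misreading.

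What remains is that adjustment for an entry measurement is available and unused, LL is undefined, and no order of reading is set.

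**Conclusion.** The point holds as a modest improvement to a secondary analysis. Adjusting follow-up MLD for reference vessel diameter would reduce its variance by 16% to 36%, worth 19% to 56% more patients for that comparison, if the correlation is 0.4 to 0.6. For late loss, the conclusion is conditional. On its usual definition, a significant result against the arm with the wider follow-up lumen is possible only when that arm's post-procedure advantage exceeds its follow-up advantage. Its chance runs from under 3% when the follow-up advantage is equal or larger, to about 60% or more under unfavourable assumptions, and is lower with provisional stenting in controls. No single figure in that range can be defended from the documents. It would be wrong to conclude that the planned t tests are invalid or that the primary conclusion is at risk.

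**What to change.** 1. Analyse follow-up MLD by ANCOVA with treatment and baseline reference vessel diameter, and name it the main continuous angiographic comparison. Add pre-procedure MLD only if it is recorded: the documents do not name it, and it is zero in occluded lesions, which are eligible.
2. Define LL in the endpoint list.
3. Report late loss by arm next to post-procedure MLD and follow-up MLD, and state in advance that it is interpreted as subordinate to follow-up MLD. Whether to keep a between-arm p value for it is a judgement; if kept, it should not be read alone.
4. Do not adjust late loss for post-procedure MLD.

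The cost is analysis wording, fixed before outcome data are seen. No extra patients or visits are needed, because reference diameter must already be assessed for eligibility; the case report form should hold its numerical value. The price is that late loss loses equal standing with follow-up MLD.

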In the context above, the present investigators attempted to identify the effects of conventional balloon angioplasty with self-expanding nitinol stent in the occlusive lesions of the infrapopliteal arteries in patients with critical limb ischemia, in the manner of collecting case data and analyzing comparatively patient groups treated with balloon angioplasty alone versus balloon angioplasty with routine stenting in a prospective multicenter randomized clinical trial.

1. **Study Objectives**

The objectives of this study are to compare directly conventional balloon angioplasty alone *versus.* balloon angioplasty with routine stenting – that is, to determine whether angioplasty with self-expanding stent is superior to conventional balloon angioplasty - in the infrapopliteal arterial occlusive lesions of critical limb ischemia patients by collecting and analyzing the cases of each patient group in a prospective multicenter randomized clinical trial, and to clarify main factors affecting mid- and long-term clinical effects of angioplasty with self-expanding stent in the infrapopliteal arteries.

Hypothesis: Balloon PTA followed by routine stenting with self-expanding nitinol stent in critical limb ischemia patients with infrapopliteal arterial occlusive lesions is superior to conventional PTA followed by provisional stenting, in the aspect of vascular restenosis rate.

1. **Study Sites and Period:**

Korean, national, multicenter prospective randomized clinical trial

Study Period: From Sept 2011 to July 2014

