   12. Significant leucopenia, neutropenia, thrombocytopenia, anemia, or known bleeding diathesis
   13. Life expectancy <1 year due to comorbidity
2. Angiographic criteria
   1. Reference segment diameter is not suitable for available stent design
   2. Previously implanted stent(s) or PTA at the same lesion site
   3. Inflow-limiting arterial lesions left untreated
3. **Sample Size Estimation**

On the assumption that the restenosis rate at 12 months after the conventional balloon angioplasty for the infrapopliteal arterial occlusive lesions in patients with critical limb ischemia is estimated approximately at 55%, whether the restenosis rate at 12 months after balloon angioplasty with routine stenting with self-expanding stent is higher than (superior to) that of the conventional balloon angioplasty alone is tested with 80% of power (20% of difference). When computed in ‘Power and Precision V4’ software program to do so, the sample size required is 89 for each group, and in consideration for drop-outs including 30% of follow up loss, the sample size (number of subjects) computed was 116 per group and a total of 232. For the statistical computation method, see the Appendix.

1. **Study Design and Methodology**

- Study design: A prospective multicenter randomized controlled trial

- Study methodology: Critical limb ischemia patients with infrapopliteal arterial occlusive or stenotic lesions at the participating centers between November 2011 and January 2015 are randomly assigned to a group of patients who will undergo provisional stenting following conventional balloon angioplasty and the other group of patients who will undergo routine stenting following conventional balloon angioplasty. Then, for each group, preoperative clinical and lesion characteristics will be investigated at baseline, the intervention procedures, immediate postoperative results, the length of hospital stay, clinical outcomes/course after discharge, and revascularization rates will be evaluated, and the restenosis rate will be angiographically examined at 12 months, followed by analyzing comparatively any factors affecting the rate.

[figure not shown]

1. **Monitoring/Laboratory and Clinical Parameters**

- Symptom diagnosis: according to Rutherford & Fontaine classification

- Preoperative clinical characteristics at baseline

- Lesion characteristics based upon the findings of imaging

- Intervention procedure related parameters

- Postoperative outcomes/course

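### The unadjusted chi-square for 12-month restenosis is valid but leaves precision unused, and the factor objective has no method that separates correlated baseline factors

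*Combined protocol and SAP*

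**What the plan says.** The efficacy section names the "Primary endpoint: Binary restenosis at 12 months" and defines it as more than 50% re-obstruction on quantitative angiography. Item 3 of that section (Statistical analysis) is the whole analysis plan:

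- Categorical outcomes, which include the primary: "Categorical variables will be expressed in percentage, and inter-subgroup comparisons will be analyzed with either Chi-square or" Fisher's exact test.
- Continuous outcomes, which include follow-up MLD: "Continuous variables will be expressed in mean ± standard deviation, and inter-subgroup comparisons will be analyzed with Student" (the t test).
- Clinical course and events: these "will be analyzed with Kaplan-Meier survival estimates, and inter-subgroup comparisons will be analyzed with log-rank test".

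No regression model, stratified test, covariate list or stratification factor appears in the protocol or its Appendix.

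On baseline data, Study Design and Methodology says that "preoperative clinical and lesion characteristics will be investigated at baseline", and the monitoring section lists "Lesion characteristics based upon the findings of imaging". The anatomical and clinical inclusion criteria require lesion length (under 8 cm), reference vessel diameter (2.0-4.5 mm), stenosis or occlusion, and Rutherford class (4-6) to be established for each patient. The background section says that balloon angioplasty does worse in long and complex lesions.

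Study Objectives adds a second aim, "to clarify main factors affecting mid- and long-term clinical effects of angioplasty with self-expanding stent in the infrapopliteal arteries". Study Design and Methodology repeats it for the restenosis rate: "followed by analyzing comparatively any factors affecting the rate". Neither place names a method.

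**The concern.** There are two separate matters, of different kinds.

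The first is efficiency. The protocol treats lesion features as prognostic and has to measure them, yet none enters the primary comparison. Adjusting for baseline variables that predict the outcome narrows the uncertainty of the treatment comparison without another patient.

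The second is interpretation. Length, diameter, occlusion and Rutherford class are not randomised and are likely to be correlated. If each is tested alone with the methods listed, a factor with no effect of its own can look important because it travels with one that has an effect. The trial could then name as main factors some that only stand in for others.

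**Working it through.** **Inputs from the documents.** Restenosis 55% on balloon angioplasty and a 20-point difference (Sample Size Estimation); 55% v 75%, two-sided alpha 0.05, 80% power, 89 per group (Appendix); 116 per group enrolled with 30% follow-up loss (Sample Size Estimation).

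**The plan's own figure.** Without continuity correction, n = [1.960 × √(2 × 0.65 × 0.35) + 0.842 × √(0.55 × 0.45 + 0.75 × 0.25)]² / 0.20² = (1.322 + 0.555)² / 0.04 = 88.1, so 89 per group. The stated size is therefore that of an unadjusted test.

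**Evaluable patients.** 116 × 0.70 = 81.2, taken as 81 per arm.

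**Two readings of the effect.** A fall in restenosis from 55% follows the sample-size text: 55% v 35%. If the Appendix's 55% v 75% is read as patency, restenosis is 45% v 25%. Both are shown.

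**Unadjusted power at 81 per arm.**
- 55% v 35%: z = [0.20 × 9 − 1.960 × √(2 × 0.45 × 0.55)] / √(0.2475 + 0.2275) = (1.800 − 1.379) / 0.689 = 0.611, power 72.9%.
- 45% v 25%: z = (1.800 − 1.322) / 0.660 = 0.725, power 76.6%.

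**Power with adjustment.** Assume that the covariates explain a share R² of outcome variance. The effective size is about 81 / (1 − R²).

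| Assumed R² | Effective n per arm | Power, 55% v 35% | Power, 45% v 25% |
|---|---|---|---|
| 0 | 81 | 72.9% | 76.6% |
| 5% | 85.3 | 75.1% | 78.7% |
| 10% | 90 | 77.4% | 80.8% |
| 20% | 101 | 82.1% | 85.2% |

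**Cross-check by simulation.** This used 4,000 replicates per setting and compared the chi-square with a likelihood-ratio test for treatment in a logistic model holding one baseline score. At 81 per arm and 55% v 35%, the chi-square stayed at 72-73%. The adjusted test gave 75%, 77%, 80% and 81% for score odds ratios of 1.5, 2.0, 2.5 and 3.0 per SD, which correspond to R² of about 4%, 10%, 15% and 20%. Monte Carlo error is about √(0.75 × 0.25 / 4000) = 0.7 points. With no treatment effect (89 per group, 55% in both, odds ratio 2.0), the rejection rates were 5.2% and 5.3%. The simulation tested the logistic treatment term, not the standardised risk difference itself.

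**Factor objective.** A binary factor with no effect was simulated with correlation 0.3-0.5 (on its underlying scale) to a lesion score with odds ratio 1.5-2.5 per SD. These values are also assumptions. It was declared significant at 5%:
- by the crude chi-square, pooled (n = 162, 45% restenosis): 10% to 51% of trials;
- by the crude chi-square, stent arm only (n = 81, 35% restenosis): 7% to 29%;
- after adjustment for the score: about 4% to 6%.

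**Room for a model**, at the conventional 10 events per parameter:
- Pooled: 81 × (0.55 + 0.35) = 73 events, or 81 × (0.45 + 0.25) = 57. This allows about 5-7 parameters.
- Stent arm: 81 × 0.35 = 28 events, or 81 × 0.25 = 20. This allows 2-3 factors.
- Treatment, length, diameter, occlusion and Rutherford class (1-2 terms) make 5-6 parameters. A full set of treatment interactions adds 4-5, giving 9-11, or between 57 / 11 = 5.2 and 73 / 9 = 8.1 events each.

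**The case against.** The strongest reply is that nothing here is an error in the primary test. That is right. A reader might infer that the unadjusted chi-square is biased or invalid; the documents do not support this, because treatment is randomised and the test matches the method behind the sample size.

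The benefit also rests on a covariate strength that the documents do not give. The only prognostic statement is one sentence about conventional balloon angioplasty, and eligibility narrows the range of lesions, which may weaken the covariates. The 20% row needs a score with an odds ratio of about 3 per SD. This stands, and it is why a range is shown.

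A reader might also treat adjustment as the cure for low power. The shortfall comes mainly from elsewhere: 116 is 89 × 1.3, whereas 89 / 0.70 gives 128. That is a separate point, and adjustment should not be used to excuse it.

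Lastly, a reader might say that the plan commits to one-at-a-time screening of factors. It does not; it names no method for that objective. What can be said is that the only tests listed anywhere are two-group comparisons, and those cannot answer the question.

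None of this argues against a near-free gain in the primary analysis, or against stating a method for a stated objective.

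**Conclusion.** The point holds as a recommended improvement. For the primary endpoint it is a missed gain in efficiency: about 2, 4-5 or 8-9 points of power at 81 evaluable per arm for assumed R² of 5%, 10% or 20%. The size depends on that assumption, on 30% loss from 116 per group, and on a true difference of 20 points; the direction of the gain needs only that the covariates are prognostic. For the factor objective it is a gap in method. The false-positive figures illustrate the risk under assumed correlations and do not forecast this trial's results. Event numbers are small enough that any factor analysis must be short and exploratory.

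**What to change.** 1. **Primary analysis.** Estimate a covariate-standardised risk difference from a logistic model with treatment, lesion length, reference vessel diameter, occlusion versus stenosis and Rutherford class. Report the unadjusted chi-square alongside. Fix the list and the coding (for example, Rutherford class as one term) before outcome data are seen, and use only values recorded before the allocated treatment could affect them. Diabetes is not named as a recorded variable, so the list should not depend on it.
2. **Follow-up MLD.** Replace the t test with ANCOVA on treatment and baseline reference diameter.
3. **Factor objective.** Use one main-effects logistic model on the pooled data with no more than about 5-7 parameters, or at most 2-3 prespecified factors if confined to the stent arm. Label it exploratory and leave out the full set of treatment interactions.
4. **Missing covariates.** State a rule in advance. Few gaps are expected, because these variables are needed for eligibility.

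The cost is analysis wording and a few lines of code, with no new measurements. The discipline required is that the covariate list and the missing-data rule are settled before outcomes are known; choosing them later would invite selective reporting.

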**Details**

The study will compare two groups (Group A versus Group B) on a collection of categories called Categories. The collection is composed of the following 2 categories: Response A and Response B.

Our focus is on the category called 'Response A'. The null hypothesis is that the proportion of subjects in this category is identical in Group A and Group B. Our intent is to disprove the null, and conclude that this proportion is different in the two groups.

The computation of sample size is based on the following assumptions and decisions.

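### Restenosis is assigned both a test of proportions and a log-rank test at p<0.05, and the plan does not say which one decides the primary endpoint

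*Combined protocol and SAP*

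**What the plan says.** Under Efficacy Evaluation Criteria/Method and Analysis Techniques, item 1 reads "Primary endpoint: Binary restenosis at 12 months". The definition is "Binary restenosis : >50% re-obstruction of the target lesion as assessed by quantitative" angiography. Study Design and Methodology plans one look: "the restenosis rate will be angiographically examined at 12 months".

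The Appendix (Details) states the hypothesis as one about proportions: "The null hypothesis is that the proportion of subjects in this category is identical in Group A and Group B". The Appendix sections on sample size, absolute proportions, alpha and tails give 89 per group for 55% versus 75%, two-tailed, alpha 0.05, 80% power.

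Item 3, Statistical analysis, first sets a rule for categorical variables: "inter-subgroup comparisons will be analyzed with either Chi-square or Fisher"'s exact test. It then adds a second list, which names "restenosis assessed based on the findings on ABI and invasive angiograms" beside symptoms, revascularization, major cardiovascular events and amputation. These "will be analyzed with Kaplan-Meier survival estimates, and inter-subgroup comparisons will be analyzed with log-rank test". A single p<0.05 criterion closes the paragraph. The text gives no primary test, no order of testing, no event-date or censoring rule for restenosis, and no window around the 12-month angiogram.

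**The concern.** Restenosis can be tested in two ways, each at 0.05, and nothing written fixes which result counts. That leaves room to claim success on whichever test is significant.

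The second test also fits the endpoint poorly. Restenosis has no observed onset and is known only at imaging. A log-rank test therefore compares when patients were imaged as well as whether they had restenosed. If imaging times differed by arm, it could reject although the 12-month proportions were equal. The log-rank list also mentions ABI, which is not part of the angiographic definition of the primary endpoint.

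**Working it through.** **1. The plan's own figure.** Inputs from the Appendix: p1 = 0.55, p2 = 0.75, two-sided alpha 0.05 (z = 1.960), power 80% (z = 0.842). With pooled p = 0.65:

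n = [1.960·√(2·0.65·0.35) + 0.842·√(0.55·0.45 + 0.75·0.25)]² / 0.20² = 88.1, rounded up to 89 per group.

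The Appendix variants also reproduce: 132 at alpha 0.01, 70 at alpha 0.10, and 70 one-tailed. The trial was sized on a two-proportion test, not on a log-rank test.

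**2. When the two tests agree.** If all N patients per arm are imaged at exactly 12 months, there is one event time. The log-rank statistic is then Pearson's chi-square × (2N − 1)/(2N). At N = 89 that factor is 177/178 = 0.994. In 20,000 simulated null trials the rejection rates were chi-square 5.1%, log-rank 4.8%, either 5.1%. The problem arises only once imaging dates vary.

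**3. When imaging dates vary.** The documents give no distribution of angiogram dates, so the timing inputs are assumptions. Both settings have no true difference between arms and scheduled angiograms around 12 months with SD 0.7 month.

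- Setting A: 81 evaluable per arm (116 × 0.70 = 81.2), 45% restenosis. Unless the row says otherwise, 40% of restenoses are found early, at months 1–11, in both arms. 2,000 trials per row.
- Setting B: 89 per arm, 55% restenosis. Unless the row says otherwise, 30% of restenoses are found early, at months 2–11, in both arms. 4,000 trials per row.

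Rejection rates are chi-square / log-rank / either, each test two-sided at 0.05.

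| Imaging pattern | Setting A | Setting B |
|---|---|---|
| Same in both arms | 4.5% / 4.8% / 6.8% | 5.6% / 5.4% / 8.9% |
| Same in both arms, no early detection | not run | 4.8% / 5.5% / 8.8% |
| Early detection 50% v 20% | 5.0% / 9.5% / 11.9% | 5.4% / 13.6% / 16.6% |
| Scheduled angiograms a quarter-month apart | 4.5% / 13% / 15% | not run |
| Half a month apart | 3.9% / 37% / 39% | 5.2% / 59% / 62% |
| One month apart | 4.6% / 83% / 85% | about 5% / 98% / 99% |

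The simulation standard error for a rate of 5% is √(0.05·0.95/2000) = 0.5 point in setting A and √(0.05·0.95/4000) = 0.3 point in setting B. Two independent tests at 0.05 would give 1 − 0.95² = 9.75%, so the 7–9% in the first two rows is near that ceiling.

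**4. Reading the table.** The second chance at significance needs no difference between arms; ordinary scatter of dates is enough. The log-rank false positive does need a difference in imaging time between arms.

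**The case against.** The best defence is that the intended primary test is clear enough. The hypothesis concerns a restenosis rate, the endpoint is binary at a fixed time, and the whole sample-size appendix compares proportions. The log-rank sentence is worded as an addition, covers clinical course, and describes restenosis partly through ABI. It can fairly be read as supplementary. This stands as an inference and lowers the severity. It does not close the gap, because no sentence says so and the same 0.05 threshold applies to both tests.

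The large figures also need care. A reader might infer that this trial would show a log-rank false positive in over 80% of null trials. The documents do not support that. Both arms share one 12-month schedule, and nothing suggests a one-month difference. If scheduled angiograms were dated at the nominal 12-month visit, such a shift would have no effect (log-rank about 5%), although unequal early detection would still give about 10%. The design figure is not reproduced in the text reviewed, so some follow-up detail may sit there.

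Two further readings are tempting but unsupported:

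- That target vessel revascularization is distorted because operators aware of the allocation re-treat on seeing the 12-month angiogram. The text says neither who decides on re-intervention, nor whether they are blinded, nor that the angiogram prompts it. Revascularization has a real procedure date and can stay under log-rank.
- That allowing Fisher's test costs power. Fisher is conventionally kept for sparse cells. At 81 per arm and a 25% rate, the expected count is 81 × 0.25 = 20, so it would not ordinarily be used.

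**Conclusion.** The point holds as a gap in the analysis plan that should be fixed. It does not invalidate the design or the sample size. The plan assigns restenosis two tests at 0.05 without naming the deciding one, and the log-rank test does not suit an outcome seen only at imaging.

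If either test may be claimed, the false-positive rate is about 7–9% rather than 5%, given scatter of about 0.7 month that is equal in both arms. With every angiogram at exactly 12 months there is essentially no inflation. The higher log-rank rates are conditional on imaging times differing between arms: in setting A about 9% for early detection of 50% v 20%, 13% for a quarter-month shift and over 80% for a one-month shift. They show how sensitive the test is and do not predict what this trial would see. The test of proportions stays near 5% in every pattern examined.

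**What to change.** - State one primary analysis: the difference in 12-month angiographic restenosis proportions between groups as randomised, by Pearson chi-square, two-sided 0.05, with a 95% confidence interval.
- Take restenosis off the log-rank list, or label time to restenosis as supportive and analyse it with an interval-censored method.
- Keep Kaplan-Meier and log-rank for outcomes with a true date: revascularization, death, MI, stroke and amputation.
- If the design figure does not already cover it, state the analysis window for the 12-month angiogram and how an earlier angiogram counts towards 12-month status.

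The cost is analysis wording only, with no added patients or visits, and the sizing already matches this test. The downside is that no significance claim could be made from time to restenosis.
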